### User Anonymity and Privacy

The MOST+ platform has been designed to maximize user privacy and choice within the social network. Participants are able control their level of identification within the network (ie, first name and/or photo, or complete anonymity). Should a participant become concerned about their privacy during their course of participation, they are able to “switch off” their profile to hide all of their past activity within “The Café” and anonymize their contributions to “Talk It Outs.” With the exception of the research and clinical team, user contributions to the network are viewable by current members of the network only. In addition, user activity (eg, posts and profile information) is not permanent within the network. That is, users’ accounts are renewed on a weekly basis through a user driven “opt-in” system, and all user activity is automatically hidden from the social network for those who choose not to renew their account. Although users are able to reactivate their account and regain their profile information at any point, all other user activity is permanently removed following a 4-day grace period during which users can reactivate their account. Users will be made aware that any user activity information that disappears from the social network is retained by the researchers for the purpose of analysis.

### Outcomes

The primary outcome variables will be intervention feasibility, acceptability, and safety. Assessment of intervention feasibility will involve reviewing a log of participants' access to, and usage of, the MOST+ platform. Access data will include the number of participants recruited and retained through the study, participants’ level of access, reasons for maintained partial access following initial intervention enrollment, and details of any full or partial withdrawals from the intervention. Usage data will include the number of log-ins, steps completed, and contributions to Talk It Out and The Café. This is the first study piloting an intervention of this nature and scale for help-seeking young people and, as such, registration and usage rates are difficult to predict. For this reason, an *a priori* criterion for the number of active users that would indicate study feasibility has not been defined.

Acceptability will be assessed at follow-up using specially designed questions administered within a semistructured feedback interview. Acceptability will be considered achieved if (1) Participants provide ratings of the MOST+ platform averaging above three out of five across feedback questions regarding ease of use, relevancy, helpfulness, and overall experience; (2) At least 60% of participants report that the MOST+ intervention provided timely, relevant, and helpful support at semistructured follow-up interview; and (3) At least 80% of respondents would recommend MOST+ to other young people experiencing difficulties.

The pilot will be considered to indicate safety of the MOST+ intervention if (1) At least 90% of participants report the online intervention to be safe via semistructured feedback interview at follow-up; (2) None of the participants experience a serious adverse event as a result of their engagement with the system during their intervention period (ie, none of the participants experience a significant deterioration in mental health or self-harm in response to intervention content, as reported by the participant or determined by treating health care professionals); and (3) There are no unlawful entries into the MOST+ system detected by study programmer during the 8-week pilot.

As shown in Table 1, all secondary outcomes will be assessed at both baseline and follow-up, with additional MOST+ user experience items assessed at follow-up. Secondary outcome variables will include self-report measures of perceived stress, psychological distress, functional impairment, mental well-being, satisfaction with life, social support and isolation, strengths use, depression, mindfulness, and components of self-determination theory. These outcomes have been chosen as they are relevant to young people’s perceptions of well-being and quality of life and may be amenable to change via the intervention. Strengths use represents a key target of MOST+ therapeutic content and will be investigated as a potential mediator of pre- to postintervention changes to other assessed indicators of psychosocial well-being. The registration survey will also include questions assessing frequency of internet use.

A number of additional quantitative and qualitative intervention feedback items will be administered within a semistructured telephone interview format at follow-up to gain a detailed understanding of areas for improvement within the system. The interview questions are based on the user experience approach as described by Bargas-Avila and Hornbaek [51]. Interviews will allow the study RA to explore six themes: overall impressions of MOST+, patterns of system use, feedback on specific aspects (eg, psychosocial interventions), Web chat and moderation, interactions with other MOST+ users (if relevant), and suggestions for system improvements.

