### Participants

Inclusion criteria for participants will reflect the real world clinical characteristics of young people accessing e-mental health support, that is, (1) Help-seeking young people with concerns about their own mental health, (2) Age of 16 to 25 years inclusive, and (3) Ability to give informed consent and comply with study procedures. By the age of 16 years, young people in Australia are considered able to make independent decisions regarding their health care [28]. An age range of 16 to 25 years reflects the agency of young people to make their own health service choices, while ensuring the age appropriateness of the therapeutic material and social networking features of the MOST+ platform. Existing eheadspace clients meeting these criteria will be eligible to use the MOST+ intervention.

Consistent with current eheadspace practice, participants will not be excluded from the study on the basis of clinical characteristics. However, the following exclusions will apply for access to the social networking component of the intervention: (1) acute risk of self-harm requiring urgent intervention (ie, suicidal ideation with a current plan and intent to enact this plan) indicated by a young person in Web chat or by endorsing screening questions 7 and 8 in the registration survey; (2) an eheadspace clinician, in consultation with a supervisor, deems participation in the MOST+ social network likely to interfere with appropriate clinical management of mental health symptoms (eg, psychosis) or increase risk of harm to self or others (see Figure 1); and (3) inability to confirm age and conduct induction via research assistant (RA) telephone contact.

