#### Accessing Enhanced Moderated Online Social Therapy

Only young people who indicate online that they understand and consent to study procedures will continue to the online MOST+ registration survey. This survey will assess outcomes at baseline and will consist of items administered within the registration process for standard eheadspace services, with additional questions included to assess all outcomes (see Table 1). This will take approximately 10 min to complete. Following this survey, all users will be granted access to real-time, clinician-delivered Web chat and user-directed psychosocial interventions (ie, partial access). Additional access to moderated peer-to-peer social networking (ie, full access) will be granted based on a three-tiered screening process designed to determine the safety and appropriateness of this component of the intervention for each user. Further details of the procedures for intervention implementation are provided in Figure 2.

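### Perceived safety and acceptability are judged only on full- and partial-access users pooled, so those thresholds can be met while users of the social network fall below them

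*Protocol article*

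**What the plan says.** The intervention has two levels of access. The section Accessing Enhanced Moderated Online Social Therapy says that after the registration survey "all users will be granted access to real-time, clinician-delivered Web chat and user-directed psychosocial interventions (ie, partial access"). The peer-to-peer network comes only with full access, after a three-tiered screening. The Participants section lists who is kept out of the network but not out of the study: "the following exclusions will apply for access to the social networking component of the intervention". The grounds are acute risk, a clinician's judgement, and failure to confirm age and complete induction by telephone.

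Outcomes then sets the success criteria. Four of them depend on what interviewees say:

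- Safety 1: "At least 90% of participants report the online intervention to be safe via semistructured feedback interview at follow-up"
- Acceptability 1: "Participants provide ratings of the MOST+ platform averaging above three out of five across feedback questions"
- Acceptability 2: "At least 60% of participants report that the MOST+ intervention provided timely, relevant, and helpful support at semistructured follow-up interview"
- Acceptability 3: "At least 80% of respondents would recommend MOST+ to other young people experiencing difficulties"

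None is split by access level. Data Analysis says that aggregated feedback will be compared with the preset criteria to decide whether the pilot succeeded.

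The other two safety criteria are zero-event rules: "None of the participants experience a serious adverse event as a result of their engagement with the system during their intervention period" and "There are no unlawful entries into the MOST+ system detected by study programmer during the 8-week pilot".

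Access level is logged as feasibility data (Outcomes), and the interview covers contact with other users where relevant. Neither feeds a threshold.

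**The concern.** A partial-access respondent rates Web chat and therapy content. A full-access respondent rates those plus the network. Their answers go into one percentage, and a favourable view of the first package can offset an unfavourable view of the second.

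This matters because of how the result will be used. The Discussion says the pilot will indicate whether to proceed to a large randomised trial of the model, and that model includes peer networking. A network that many users find uncomfortable or unhelpful, without causing an attributable serious adverse event or a security breach, would show up only in these four criteria. They are also the ones that pooling can dilute.

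**Working it through.** **No figure to reproduce.** The thresholds are fixed cut-offs. The target of about 250 is justified qualitatively under Sample Size, with no response rate, dropout rate or access split.

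**Inputs.** The thresholds come from Outcomes. The full-access share of respondents, f, and all response rates below are assumptions.

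**Step 1: dilution.** The pooled rate is f × p_full + (1 − f) × p_partial. The lowest full-access rate that still meets threshold T is

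p_full = (T − (1 − f) × p_partial) / f.

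For T = 0.90 and p_partial = 1:

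- f = 0.5: (0.90 − 0.50)/0.5 = 0.800
- f = 0.7: (0.90 − 0.30)/0.7 = 0.857
- f = 0.9: (0.90 − 0.10)/0.9 = 0.889

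The same formula for the other criteria gives:

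| Criterion | Partial-access assumption | f = 0.5 | f = 0.7 | f = 0.9 |
|---|---|---|---|---|
| 90% safe | 100% | 80.0% | 85.7% | 88.9% |
| 90% safe | 95% | 85.0% | 87.9% | 89.4% |
| 80% recommend | 100% | 60.0% | 71.4% | 77.8% |
| 60% timely, relevant, helpful | 100% | 20.0% | 42.9% | 55.6% |
| Mean above 3 | mean of 4 | 2.00 | 2.57 | 2.89 |

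For the mean, the full-access average need only exceed the value shown.

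In counts: if all 250 were interviewed, 225 must answer safe, so 25 may answer otherwise, and all 25 may be full-access users. With 125 full-access users, that leaves 100/125 = 80%.

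**Step 2: chance of passing safety criterion 1.** Assume 150 respondents, with true safe rates of 85% in full access and 98% in partial access. The pooled rule needs 135 of 150. The chance is P(X + Y ≥ 135), with X ~ Bin(150f, 0.85) and Y ~ Bin(150(1 − f), 0.98). The comparison applies 90% to the full-access group alone.

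| f | Expected pooled rate | Pooled rule passes | Full-access-only rule passes |
|---|---|---|---|
| 0.5 | 0.5 × 0.85 + 0.5 × 0.98 = 0.915 | 0.80 | 0.11 |
| 0.7 | 0.7 × 0.85 + 0.3 × 0.98 = 0.889 | 0.39 | 0.07 |
| 0.9 | 0.9 × 0.85 + 0.1 × 0.98 = 0.863 | 0.11 | 0.05 |

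The gap is large at an even split and small when nearly all respondents have full access.

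**Step 3: the zero-event rule.** One attributable event fails the criterion whatever the number of partial-access users. With 125 full-access users and a true attributable event rate of 1%, the chance of seeing none is 0.99^125 = 0.285. Adding partial-access users without events does not change it. Safety criterion 3 concerns the system and has no participant denominator.

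**The case against.** The strongest objection is that the pooled verdict is the right one for the stated aim. The Introduction frames feasibility, acceptability and safety for young people who have accessed eheadspace, not for those cleared for the network. Duration of Access treats everyone as enrolled in MOST+ whatever their access level, and Sample Size recruits irrespective of telephone contact so as to mirror real use. Tiered access is part of the intervention. This stands, and it is why the pooled verdict should stay. Making full-access users the only deciding group would condition the verdict on selection after enrolment and drop the highest-risk users from it.

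Second, the size may be small. Users who cannot be reached by telephone stay on partial access, and Sample Size expects them to be hard to retain. Interviewees therefore probably lean towards full access, where the floor is only about 1 point (f = 0.9) or 4 points (f = 0.7) below 90%. This also stands as a limit on size. It does not settle the matter, because the share is unknown and reachable users can also be kept on partial access on clinical grounds.

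Third, reporting by access level could be left to an analysis plan that is not shown. That is fair for descriptive tables. The success rule itself, however, is fixed in this article, and it is pooled.

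A reader might go further and infer that MOST+ could be declared safe while harming network users. The document does not support that. The three safety criteria must all be met, one attributable serious adverse event fails the pilot, and Harms treats attributable deterioration as an unacceptable safety risk. Nor can it be said that no partial-access user has seen the network, since Acute Risk allows return from full to partial access. The protocol also does not call the network the riskiest component; that is an inference from the screening placed on it.

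**Conclusion.** The point holds for perceived safety (safety criterion 1) and the three acceptability criteria, and for nothing else. Each can be met on the pooled sample while network users fall below the threshold. For the 90% rule the possible shortfall is 10 points at an even split, 4.3 points at 70% full access and 1.1 points at 90%. These figures assume that every partial-access respondent answers favourably, and the shares themselves are assumed. With partial access at 95%, the shortfalls fall to 5.0, 2.1 and 0.6 points.

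The pooled criteria are a defensible verdict on the tiered service as delivered. They do not by themselves support a statement about the social-networking component. This is a cheap improvement rather than an error that undermines the pilot.

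**What to change.** 1. Keep the pooled verdict on all four criteria for the tiered service as delivered.
2. Also apply safety criterion 1 and the three acceptability criteria, at the same thresholds, to respondents who ever had full access. Include those later returned to partial access, so that people moved out of the network are not lost from the group that experienced it.
3. Report numerators, denominators and confidence intervals for that group, with partial-access results alongside.
4. State in advance that the social-networking component will not be described as perceived to be safe or acceptable unless the ever-full-access group meets the thresholds.
5. Leave safety criteria 2 and 3 as they are.

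Access level is already logged, so the change costs a sentence or two in Outcomes and a stratified table. The price is precision. At a 90% rate, the approximate 95% half-width is 1.96 × √(0.9 × 0.1/150) = 4.8 points with 150 respondents and 1.96 × √(0.9 × 0.1/75) = 6.8 points with 75.

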### Sample Size

The majority of young people who access eheadspace make use of the service on one or two occasions only, and a primary objective of MOST+ is to facilitate responsive and effective intervention within this short window. To mirror likely real-world implementation of the MOST+ model, we will also be recruiting young people to the online intervention regardless of whether they can be contacted via telephone within the first week of study enrollment (see Figure 2). Although follow-up periods will be tailored to participants’ initial period of intervention engagement, it is likely to be challenging to retain participants who have engaged only briefly and/or were unable to be contacted via telephone at enrollment. A sample size of approximately 250 participants will therefore be necessary both to provide an adequate buffer against attrition during the study and to ensure that there is a sufficient number of active users of MOST+ for the social networking aspect of the intervention to function effectively throughout the 8-week pilot.

### Data Collection and Management

All participants will receive one AUS $30 voucher as reimbursement for their time in completing registration and another for completing follow-up. Follow-up assessment will occur approximately 4 days after initial account deactivation (ie, 4 days after a user has opted not to renew their account for an additional week). For those participants who maintain active enrollment across the intervention period, follow-up will occur as soon as possible following conclusion of the pilot. The exact duration of follow-up cannot be estimated as the number of participants enrolled in MOST+ will not be capped. To minimize attrition, participants will receive a short service message notification that their online follow-up survey is due and will be able to complete survey items either online or via telephone. Participants who do not complete the follow-up survey will be reminded via phone call by an RA. Both baseline and follow-up assessments will be designed to minimize participant burden, while ensuring that requirements for the eheadspace Minimum Data Set (MDS; ie, routine data about each occasion of service) are met.

The MOST+ system and data generated through participants’ use of the online platform will be hosted on a secure University of Melbourne Web server. Data collected via online surveys and telephone interviews will be entered electronically and also centrally stored on a University of Melbourne Web server. At the conclusion of the study, this data will be exported and stored securely in a password protected file on the server at Orygen. In addition, data collected as part of eheadspace MDS requirements will be provided to headspace at the conclusion of the study. For each MOST+ account, clinical content collected via Web chat and surveys will be copied into an eheadspace account to ensure continuity of care should the participant continue using eheadspace services post trial.

All of the PIs will have access to the final pilot dataset for the purpose of characterizing the participant sample, characterizing the activity within the MOST+ system, and testing the study hypotheses. The study RAs will also have access to the dataset for the purpose of data entry and management. Expert moderators and eheadspace clinicians working within MOST+ will have access to individual and aggregated usage data available within the moderator interface.

Given the relatively small scale, brief duration and primary aims of assessing the feasibility, acceptability, and safety of the intervention, an independent data safety monitoring committee will not be established for this study.

### Data Analysis

Frequency, duration, and patterns of use of MOST+ will be tracked in real time. Up-to-date charts will be visible on demand to MOST+ staff via the moderator interface of the online platform. This data will be aggregated into simple descriptive statistics to characterize participants’ use of the intervention. In addition, overall rates of MOST+ participation and aggregated data from the user feedback questionnaire will be compared with the *a priori* acceptability and safety criteria to determine success of the pilot. Supplementary paired samples *t* tests will be conducted to assess pre- to postintervention changes to outcomes. System usage will be examined as a covariate.

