#### Duration of Access

Regardless of level of access, all participants will be enrolled in the MOST+ intervention for 1 week, with the option to extend their enrollment on a weekly basis across the study intervention period. Thus, participants’ period of enrollment in the intervention will range from a minimum of 1 week to a maximum of 8 weeks. Participants will be able to reactivate an expired account at any time during the study intervention period, and this will be treated as a second episode of care. Following the conclusion of the pilot study, participants will be redirected to eheadspace if they attempt to log into the MOST+ platform. See Figure 3 for examples of participants’ possible enrollment time lines, with each colored line representing a different potential time line over the duration of the pilot.

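### Usage is the only covariate planned for pre-post change, but it builds up with enrolled time and follow-up timing depends on that same time, so a usage association cannot be separated from elapsed time

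*Protocol article*

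**What the plan says.** All references are to the Methods of the protocol article.

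- **Test of change (Data Analysis):** "Supplementary paired samples *t* tests will be conducted to assess pre- to postintervention changes to outcomes".
- **Role of usage (Data Analysis, next sentence):** "System usage will be examined as a covariate". No model is named for this, and no other covariate is mentioned.
- **Usage measure (Outcomes):** counts of log-ins, completed steps and contributions to the two social areas.
- **Length of enrollment (Duration of Access):** "participants’ period of enrollment in the intervention will range from a minimum of 1 week to a maximum of 8 weeks", "with the option to extend their enrollment on a weekly basis across the study intervention period". An expired account can be reactivated, which counts as a second episode of care.
- **Timing of follow-up (Data Collection and Management):** "Follow-up assessment will occur approximately 4 days after initial account deactivation". For those who stay enrolled throughout, "follow-up will occur as soon as possible following conclusion of the pilot". The section adds that the exact length of follow-up cannot be estimated. The Sample Size section confirms that follow-up is fitted to each person's first period of engagement.
- **Design (Abstract; Study Design and Setting):** one uncontrolled group, recruited during the first 4 weeks of an 8-week intervention period.

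**The concern.** Three quantities move together by design: weeks enrolled, total usage, and time from baseline to the second measurement. People who seek help when distressed may improve, or change in other ways, with time alone. Those measured later have had more time for that to happen and have also had more time to accumulate log-ins and steps. With usage as the only covariate and no control group to show the time trend, the usage coefficient absorbs part of that trend.

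Two smaller points add to this. The only inferential test named has no place for a covariate, so the usage analysis has no stated model. And because follow-up is triggered by the first deactivation while accounts can be reactivated, a count taken over the whole pilot could include use that came after the outcome was measured.

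At stake is how any reported link between usage and improvement is read. The pilot's criteria for success are not at stake.

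**Working it through.** **1. The interval, from the article's own figures.**

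- Shortest: 1 week enrolled plus about 4 days = 7 + 4 = 11 days.
- Longest, for a first-day entrant who renews throughout: 8 × 7 = 56 days, plus a delay that is not specified. If that delay were also 4 days, the interval would be 60.
- Ratio: 56/11 = 5.1; 60/11 = 5.5.
- Entrant at the end of week 4: at most 4 × 7 = 28 days plus delay (32 if the delay is 4 days); 28/11 = 2.5, 32/11 = 2.9.

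The interval is thus set partly by the participant and partly by entry date.

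**2. How time passes into the usage term.** Suppose usage has no effect and change depends on time only. Then

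corr(usage, change) = corr(usage, time) × corr(time, change).

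The product is zero only if one factor is zero. Counts that build up during enrollment make the first factor positive. The second is unknown.

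**3. Size under assumptions.** The article gives no SD of change, time trend, log-in rate or renewal pattern, so all of the following are assumed: 125 completers; residual SD of change 6 points; 3 log-ins per week on average; weeks enrolled 1 to 8 with probabilities 0.50, 0.20, 0.10, 0.08, 0.05, 0.04, 0.02, 0.01; a linear fall of *s* points per week; no usage effect.

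- Weeks *W*: mean 2.23, mean square 7.79, variance 7.79 − 2.23² = 2.82, SD 1.68.
- Usage variance, with *c* the between-person coefficient of variation of the log-in rate: 3 × 2.23 + 9 × (2.82 + *c*² × 7.79).
- *c* = 0: variance 32.0, so corr(usage, *W*) = 3 × 1.68/√32.0 = 0.89. For *c* = 0.7, 1.0 and 1.4 it is 0.62, 0.50 and 0.39.
- corr(*W*, change) = 1.68*s*/√(36 + 2.82*s*²). At *s* = 0.5 this is 0.139.
- Example, *c* = 0 and *s* = 0.5: *r* = 0.89 × 0.139 = 0.123. The expected *t* is *r*√125/√(1 − *r*²) = 1.39, which gives a two-sided 5% rejection rate of about 28%.

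Rejection rate for usage when time is left out (same formula; simulation agrees to within about 2 percentage points):

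| Variation in log-in rate, *c* | *s* = 0.25 | *s* = 0.5 | *s* = 1.0 |
|---|---|---|---|
| 0 (one shared rate) | 11% | 28% | 79% |
| 0.7 | 8% | 16% | 47% |
| 1.0 | 7% | 12% | 33% |
| 1.4 | 6% | 9% | 22% |

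With elapsed time in the model, simulation gives about 5% in every cell, whether usage enters as a total or per enrolled week.

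**4. A different assumed shape.** With improvement that levels off (total 0.3 to 0.8 SD of change, time constant 14 to 56 days, weekly renewal probability 0.3 to 0.7, 125 or 250 completers), the rate without time is about 5% to 22%, mostly in the direction of more use, more improvement. With time added it is about 4% to 6.5%. If faster improvers stop renewing sooner, the mean correlation between usage and improvement turns slightly negative, about −0.03.

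**The case against.** The strongest reply has four parts.

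*The two sentences can be separate analyses.* Nothing says that usage enters the t test; a regression of change on usage would fit the text, and an article may leave the exact model to an analysis plan. This stands. A reader might infer that the planned analysis is impossible to run. The text does not support that; the wording is loose. What remains is that the article does fix usage as the covariate and does fix a follow-up date tied to enrollment, and that combination causes the problem.

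*The inputs are assumed.* This also stands. A reader might infer that a false dose-response is likely. The high rates need everyone to share one log-in rate and an unbroken linear fall. When rates vary between people, as is plausible with partial and full access, they drop sharply, and the direction can reverse.

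*The variable interval is deliberate and disclosed.* True, and the design need not change. Disclosure does not put the interval into the analysis.

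*Little hangs on it.* The tests are labelled supplementary and serve a secondary aim. The Discussion rests progression to a randomized trial on feasibility, acceptability and safety. A reader might infer that the usage result would drive that decision; no section says so.

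A reader might also want a figure for bias from analyzing completers only. The Sample Size section does expect brief users to be harder to retain, but the article gives nothing from which to size such a bias.

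**Conclusion.** The concern holds in limited form. As the article stands, a usage-change association could not be told apart from change over elapsed time, because usage counts and the interval to follow-up (about 11 days to 56 days plus an open delay) both grow with enrolled weeks, there is no control group, and usage is the only covariate named. That much follows from the article itself.

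The size does not. Under the assumptions shown, the false-positive rate for usage lies anywhere from nominal to about 79%, and at or below about 22% if improvement levels off. The finding that rests least on particular inputs is that adding elapsed time brought the rate back to about 5% in the settings where it was tried. Adjustment for time does not remove self-selection into heavier use, so the result would still not be causal.

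This is worth correcting because the remedy is cheap. It does not threaten the pilot's primary conclusions.

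**What to change.** Keep the paired t tests as an unadjusted description of change. Replace the usage sentence with:

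*The association of usage with outcome will be examined by regressing the follow-up score on baseline score, usage per enrolled week counted up to the follow-up date, and days from baseline to follow-up, reported with 95% CIs as exploratory and non-causal.*

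If a mixed model on all enrolled participants is used for mean change, code time as 0 at baseline and as actual days at follow-up. A person-level days-to-follow-up covariate would not work there: it does not exist for people without follow-up, so it would drop the participants the model is meant to keep. With time coded by visit they still contribute their baseline value.

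**Cost.** Wording only; it uses usage logs, baseline scores and survey dates, with no new assessment. The exposure becomes intensity of use rather than total use. Total use can be shown alongside, also adjusted for days, with a wider interval: the standard error grows by about 1/√(1 − ρ²), where ρ is the correlation of total use with elapsed time. That is 1.15 at ρ = 0.5, 1.25 at 0.6 and 2.2 at 0.89. The wider interval correctly reflects how little the data can separate the two.
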